## Abstract

**Background:**

The innate immune receptor RIG-I detects viral RNA within the cytosol of infected cells. Activation of RIG-I leads to the induction of antiviral cytokines, in particular type I interferon, the inhibition of a T(H)17 response as well as to the suppression of tumor growth. Therefore, RIG-I is a promising drug target for the treatment of cancer as well as multiple sclerosis. A specific ligand for RIG-I is currently in preclinical testing. The first-in-human trial will need to be carefully designed to avoid an overshooting cytokine response. Therefore, the ResI study was set up to analyze the human immune response to standard treatment with recombinant interferon-beta to establish biomarkers for safety and efficacy of the upcoming first-in-human trial investigating the RIG-I ligand.

**Methods/Design:**

ResI is a single center, prospective, open label, non-randomized phase I clinical trial. Three different cohorts (20 healthy volunteers, 20 patients with RRMS and ongoing interferon-beta treatment and 10 patients starting on interferon-beta) will receive standard interferon-beta-1a therapy for nine days. The study will be conducted according to the principles of the german medicinal products act, ICH-GCP, and the Declaration of Helsinki on the phase I unit of the Institute of Clinical Chemistry and Clinical Pharmacology and in the Department of Neurology, both University Hospital Bonn. Interferon-beta-induced cytokine levels, surface marker on immune cells, mRNA- and miRNA-expression as well as psychometric response will be investigated as target variables.

**Discussion:**

The ResI study will assess biomarkers in response to interferon-β treatment to guide the dose steps within the first-in-human trial with a newly developed RIG-I ligand. Thus, ResI is a biomarker study to enhance the safety of the clinical development of a first-in-class compound. The data can additionally be used for the development of other therapies based on type I interferon induction such as TLR ligands. Moreover, it will help to understand the interferon-beta induced immune response in a controlled *in vivo* setting in the human system.

**Trial registration:**

clinicaltrials.gov ID NCT02364986

## Background

Retinoic acid inducible gene-I (RIG-I) is a pattern recognition receptor (PRR) of the innate immune system, broadly expressed in immune - but also in non-immune cells, including tumor cells [1–3]. RIG-I is a sensor for pathogenic RNA, detecting 5’-triphosphorylated RNA (3pRNA) in the cytosol of infected cells [4, 5], crucially important to protect from different RNA viruses [2, 6]. Activation of RIG-I leads to a broad antiviral immune response, including strong induction of type I interferon (IFN), to eradicate the invading pathogen. A potent benefit of therapeutic activation of RIG-I was described recently in different indications: i) 3pRNA suppresses tumor growth by triggering apoptosis specifically in tumor but not in non-malignant cells as well as by inducing an anti-tumor immune response, including type I IFN induction and NK cell activation [7–10]. ii) Activation of RIG-I inhibits the viral replication and is therefore protective in viral diseases such as Hepatitis B [11] and influenza infection (unpublished data). iii) Activation of RIG-I in mice with induced experimental autoimmune encephalomyelitis, the animal model for MS, significantly ameliorates autoimmune inflammation, decreases demyelination and improves the clinical outcome by repressing the maintenance and expansion of T(H)1 and T(H)17 cells [12]. As in all these indications an unmet therapeutic need exists, triggering of RIG-I by a synthetic short 3pRNA-ligand is a promising new therapeutic approach with broad clinical implication [1]. A specific RNA ligand for RIG-I is currently under preclinical evaluation. Even though we identified relevant animal species for preclinical toxicity testing (unpublished data) the RIG-I ligand bears characteristics making increased caution in the first-in-human trial necessary as outlined in the European Medicines Agency (EMA) “Guideline on strategies to identify and mitigate risks for first-in-human clinical trials with investigational medicinal products” (EMEA/CHMP/SWP/28367/07): i) as first-in-class compound it is a novel mechanism of action, involving multiple signalling pathways [13] ii) it is an activating mechanism and iii) the RIG-I ligand acts on the immune system inducing the release of antiviral and pro-inflammatory cytokines [1, 4, 5]. To minimize the probability of a possible overshooting cytokine induction in the first-in-man phase I trial, thorough preclinical testing needs to be performed. In addition, biomarkers indicating activity or toxicity of RIG-I agonisation would be of great value to safely guide the first-in-man trial. Moreover, such biomarkers could be used as surrogate parameter to gather first data on the potential efficacy of a RIG-I ligand, starting in the first-in-man trial and later on in more advanced stages of the clinical development. Type I IFN serum level as well as the dependent immune response will bear suitable information for dose guiding of the RIG-I ligand since type I IFN is a key cytokine induced by RIG-I [4, 14]. To give an orientation on a type I IFN level that is potentially therapeutic active, the effect of standard interferon treatment as routinely applied in multiple sclerosis can be used. As soon as the type I IFN response induced by a certain dose of the RIG-I ligand reaches the levels induced by standard treatment with recombinant IFN-β, this level can be regarded as a potentially effective dose. With this information the dose steps within the phase I study can be carefully guided, side effects better monitored and there will be no need to explore the maximal tolerable dose.

For this purpose, the ResI study was set up as a clinical trial aiming to establish a biomarker for the safety and efficacy of the RIG-I ligand, a novel therapeutic entity currently in preclinical testings. Since studies of the RIG-I ligand will start in healthy volunteers and will be continued in MS patients both populations are included in this study as they could show significant differences in response to IFN-β. Additionally, this comprehensive, prospective analysis of the IFN-β dependent immune activation and changes in miRNA expression in this controlled setting will help to understand the physiological response to IFN-β in healthy volunteers and in MS patients.

## Methods/Design

ResI is a single center, prospective, open label, non-randomized phase I clinical trial. Three different cohorts (healthy volunteers, patients with RRMS and ongoing IFN-β treatment and patients with RRMS starting on IFN-β treatment) will receive three applications of standard IFN-β therapy for nine days. As a comparison between pre- and post-treatment is performed, no placebo group is planned. The study will be conducted according to the principles of the german medicinal products act, ICH-GCP, and the Declaration of Helsinki on the phase I unit of the Institute of Clinical Chemistry and Clinical Pharmacology and in the Department of Neurology, both University Hospital Bonn. The local ethics committee and the German competent authorities (Federal Institute for Drugs and Medical Devices) already approved this study. The Clinical Study Core Unit will perform the clinical procedures, monitoring, safety management, data management, and data analysis of the study. The Institute of Clinical Chemistry and Clinical Pharmcology, that includes the central laboratory of the University Hospital Bonn will perform the routine as well as experimental laboratory analysis.

### Primary objective

The primary objective of this phase I trial is to determine IFN-β protein level as well as IFN-β-dependent mRNA and protein expression in healthy volunteers and in RRMS patients continuing or starting on IFN-β treatment (including CXCL10, MxA, RIG-I).

### Secondary objectives

Secondary objectives of this trial are the analysis of the miRNA- and gene-expression pattern in response to recombinant IFN-β in peripheral blood mononuclear cells and serum of healthy volunteers as well as RRMS patients, the comparison of the response to IFN-β between healthy volunteers, patients with RRMS naïve to IFN-β treatment and RRMS-patients with established IFN-β treatment, correlation of side effects of IFN-β treatment with immune- or miRNA-response to IFN-β. Potential central nervous adverse drug effects such as emotional changes associated with IFN-β treatment (depression, anxiety, impulsivity) will be assessed by psychometric testings and noninvasive neuroimaging techniques.

### Inclusion criteria

Three different cohorts will be studied: 1.) Healthy volunteers naïve for IFN-β treatment. 2.) patients with relapsing-remitting MS (RRMS) according to McDonald's criteria and baseline expanded disability status scale (EDSS) score from 0 to 6.0 starting on IFN-β treatment according to routine clinical criteria. 3.) Patients as described above but already on IFN-β treatment. Additional inclusion criteria applicable for all individuals in this study: age between 18 and 65 years, adequate bone marrow-, renal-, hepatic- and clotting-function. Male and female patients with reproductive potential have to use an approved contraceptive method and a negative serum pregnancy test must be obtained prior to treatment start in female patients with childbearing potential. All individuals need to have signed the informed consent form.

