### Exclusion criteria

The main exclusion criteria comprise of: known allergy or hypersensitivity to IFN-β or ingredients of the injection solution; condition or disease which at the investigator’s discretion do not fit with the study; known or persistent abuse of medication, drugs or alcohol; current use of cortisone preparation; subjects with reproductive potential who do not accept to use contraception during the trial and 3 months thereafter or women who are pregnant or breast-feeding; prior malignancy except for adequately treated carcinoma in situ of the cervix or non-melanoma skin cancer unless prior malignancy was diagnosed and definitively treated at least 5 years previously with no subsequent evidence of recurrence the subject at the discretion of the investigator; prior chemotherapy, systemic or local treatment with DNA-damaging and immune-modulating agents, tyrosine kinase inhibitors or anti-angiogenic agents for any cancer; history of major depression, suicide attempt in the past, ongoing suicidal thoughts; history of epileptic seizures under medical therapy with antiepileptic drugs; cardiac insufficiency (NYHA III or IV) cardiomyopathy, significant cardiac dysrhythmia, unstable or advanced ischemic heart disease, or significant hypertension at rest (blood pressure > 180/110 mmHg); HIV, Hepatitis B or C infection or any relevant infectious disease which might interfere with the study procedures and results (at the discretion of the investigator).

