### Therapy

Three different cohorts will be treated in this study: healthy volunteers, patients with RRMS and ongoing IFN-β treatment and patients with RRMS starting on IFN-β treatment. Patients and healthy volunteers will receive three doses of 44 μg open-label Interferon-β-1a (Rebif®) within nine days as recommended in the standard treatment schedule. MS patients already on IFN-β treatment will only receive one dose of IFN-β while included in this study. Dose modification or adjustments for either group are not intended by the trial protocol. After the study is finished MS patients will be treated at the discretion of the responsible physician.

At or before the screening visit, each patient has to provide written informed consent to the study. The screening consists of reviewing inclusion and exclusion criteria, demographic variables, medical history, concomitant medication, physical and neurological examination and vital signs, electrocardiogram (ECG) and laboratory tests are obtained by a study nurse and the treating physician. MRI, EDSS scoring and psychometric tests are performed. Laboratory tests include complete blood count, serum chemistry, coagulation, drug screening, pregnancy test and urine analysis.

At baseline visit vital signs and ECG as well as the occurrence of adverse events and changes of the concomitant medication are documented. Screening and baseline visit are performed within 14 days. Then IFN-β-1a treatment is started and blood for the analysis of cytokine serum levels, miRNA- and mRNA-expression as well as experimental immune evaluation is collected at five different times within 24 h. Thereupon, the study is finished for MS patients that have been already on IFN-β treatment. Healthy volunteers as well as MS patients that have been started on IFN-β will continue with study visits at days 3, 5 and 8 with documentation of adverse events and concomitant medication and collection of further blood samples for analysis of immune activation. At day nine healthy volunteers as well as MS patients will have the final visit with the same assessments as described for the screening and baseline visit, including magnetic resonance imaging (MRI) assessment. Additional, blood for analysis of immune activation is collected.

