### Statistical analysis

The **sample size** is set on 20 healthy volunteers and 20 patients with established IFN-β treatment and 10 MS patients naïve to IFN-β treatment. Since this is a study to gain information about the distribution of the expression values in these patients, this sample size is not based on statistical considerations.

**Primary target variables** of the study is the estimation of changes in serum level of type I IFN and type I IFN-dependent proteins (e.g. CXCL10) as well as of changes in mRNA expression of type I IFN-dependent genes (e.g. CXCL10, MxA and RIG-I) after a dose of IFN-β treatment in healthy volunteers and in patients with RRMS. For this purpose, the median of the levels will be calculated separately for the two study groups. 95 % confidence intervals for the medians will be calculated using bootstrap. As additional descriptive parameters mean, standard deviation, minimum, maximum and the quartiles of the distribution will be calculated for each group and variable. A comparison of the expression levels between patients and controls will be performed with a two-sided Mann–Whitney-Wilcoxon test. These tests are regarded as descriptive analysis, their result are reported as p-values.

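### In the cohort already on IFN-β the pre-dose value is an on-treatment value, so its change, and its contrast with the naive cohorts, carries marker-dependent carry-over from earlier injections

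*Protocol article*

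**What the plan says.** - **Who enters.** In the protocol article, Inclusion criteria, the healthy cohort is "Healthy volunteers naïve for IFN-β treatment". The second cohort is RRMS patients starting IFN-β. The third is "Patients as described above but already on IFN-β treatment". Under Statistical analysis the sizes are 20 healthy, 10 naive and 20 established patients.
- **What limits earlier exposure.** No printed criterion does so for the third cohort. The nearest exclusion, "systemic or local treatment with DNA-damaging and immune-modulating agents, tyrosine kinase inhibitors or anti-angiogenic agents for any cancer", concerns cancer treatment.
- **What is given.** Therapy fixes the study product and dose: "Patients and healthy volunteers will receive three doses of 44 μg open-label Interferon-β-1a (Rebif®) within nine days". It then adds: "MS patients already on IFN-β treatment will only receive one dose of IFN-β while included in this study". Blood is taken at five times within 24 h.
- **Timing before the dose.** "Screening and baseline visit are performed within 14 days". Nothing printed says whether routine injections go on during that window.
- **What is estimated.** Under Statistical analysis the primary target begins with "estimation of changes in serum level of type I IFN and type I IFN-dependent proteins (e.g. CXCL10" being the protein example), and goes on to mRNA changes. The opening of Methods/Design explains that there is no placebo group because pre- and post-treatment values are compared.
- **What is compared.** Secondary objectives set the response of healthy volunteers and naive patients against that of "RRMS-patients with established IFN-β treatment". Statistical analysis compares patients with controls by a two-sided Mann-Whitney-Wilcoxon test, reported descriptively.

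**The concern.** A change from baseline measures the effect of a dose only if the baseline is free of the effect of earlier doses, or carries it to a known and equal extent. In the two cohorts not yet treated the baseline is untreated. In the third it contains whatever remains from the previous injections. Residual stimulation raises the starting value and so shrinks a relative change, even when the response to each dose is the same.

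At stake is the reading of the comparison between cohorts. The Discussion says that both populations are included to find out whether they respond differently to IFN-β. A smaller change in treated patients could be taken for tolerance or a disease effect when it is only a raised baseline. Statistical analysis also speaks of two study groups. If the patients are pooled, the treated cohort supplies 20 of 20 + 10 = 30 patients and dominates that side of the test.

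**Working it through.** There is no planned figure to reproduce: the article states that the sample size has no statistical basis, and it gives no effect size, SD, marker half-life or injection interval. The check is therefore an illustration, and every kinetic input is an assumption.

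**Model.** The untreated level is 1. Each dose adds F − 1 units, which decay with half-life h. Doses come regularly every t hours.

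- Pre-dose level: P = 1 + (F − 1)/(2^(t/h) − 1)
- Apparent fold change: (P + F − 1)/P

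**Worked case.** F = 5, t = 48 h, h = 24 h: P = 1 + 4/(4 − 1) = 2.33, and the fold change is 6.33/2.33 = 2.71. With h = 48 h: P = 1 + 4/(2 − 1) = 5, and 9/5 = 1.80. With h = 6 h: P = 1 + 4/255 = 1.02, giving 4.94.

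**Apparent fold change when the true response is 5-fold throughout:**

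| Half-life | last dose 48 h ago | 72 h | 168 h |
|---|---|---|---|
| 6 h | 4.94 | 5.00 | 5.00 |
| 12 h | 4.16 | 4.76 | 5.00 |
| 24 h | 2.71 | 3.55 | 4.88 |
| 48 h | 1.80 | 2.25 | 3.88 |
| 72 h | 1.51 | 1.80 | 3.01 |

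**How much of the spread is the interval?** With intervals of 48, 72 and 168 h mixed equally and half-lives of 6 to 72 h, the interval explains 0–54% of the variance of the log fold change at a between-subject SD of 0.3, 0–29% at SD 0.5 and 0–14% at SD 0.8. With daily steps from 24 to 168 h the maximum is 57%, at SD 0.3.

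**Effect on the between-group test.** Simulation: 20 untreated-baseline against 20 treated participants, identical true response per dose, mixed intervals, 2,000 runs, with 0.05 assumed as threshold because the article sets none. Share of runs with p < 0.05:

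| Half-life | SD 0.3 | SD 0.5 | SD 0.8 |
|---|---|---|---|
| 6 h | 4.7% | 5.7% | 4.7% |
| 12 h | 11.4% | 7.7% | 6.1% |
| 24 h | 79.9% | 43.9% | 22.5% |
| 48 h | 100% | 96.9% | 69.5% |
| 72 h | 100% | 99.9% | 92.0% |

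**Dependence on scale.** The article does not say whether change is a ratio or a difference. In this additive model the difference is always F − 1 = 4, so only the ratio is distorted. If instead every dose drives the marker to the same peak, the difference shrinks too. Take an assumed peak of 16, a 24 h half-life and a last dose 48 h earlier: the baseline is 1 + 15/4 = 4.75, the ratio 16/4.75 = 3.4 and the difference 16 − 4.75 = 11.25, against 16 and 15 from an untreated baseline. No single scale is safe without knowing the marker.

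**The case against.** **This is a condensed article.** Visit timing relative to the last injection, and the earlier product and dose, are details that a full protocol may fix. That stands, and a missing minimum treatment duration is not held against the text. But the pre-dose control, the change-based target and the contrast with naive cohorts are printed. A fixed interval would remove the variation between patients, not the raised baseline: with every patient at 48 h and a 24 h half-life, the ratio is still 2.7 instead of 5.

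**The on-treatment state is intended.** It is: Primary objective includes patients continuing IFN-β, and Secondary objectives ask for naive against established. What that contrast does not need is uncontrolled recency, product and dose of the earlier exposure.

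**The plan works largely with levels.** Statistical analysis takes medians of levels and tests expression levels, and Background and Discussion judge the RIG-I ligand against the levels reached under standard treatment. This carries weight. A reader might infer that the RIG-I reference would be set from this cohort's change. The text does not say so, and the 10 patients starting IFN-β give an MS response from an untreated baseline.

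**Some of the data are already collected.** Concomitant medication and medical history are taken at screening, so product and dose may well be on file. Hours since the last injection is the likely gap.

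**Stronger readings.** A reader might infer that the change in this cohort mostly reflects the injection interval, or that it does not estimate a response at all. The documents support neither. They give no kinetics, the interval explains anything from none to 57% of the variance in the illustration, and at a 6 h half-life the distortion all but vanishes.

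**Conclusion.** The point holds in a limited form. As printed, the change in the treated cohort is confounded by time since, and type and dose of, earlier IFN-β, to an extent that differs by marker. Under the assumed 5-fold response and 48 h interval the apparent fold change runs from 4.9 (6 h half-life) through 2.7 (24 h) to 1.8 (48 h). The chance of an artefactual difference from an untreated-baseline cohort ranges from about the nominal 5% to near certainty over the assumed half-lives.

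This rests on assumed half-lives, intervals, response and SD, and on change being read as a ratio. The direction (a smaller relative change from a raised baseline) needs only that some stimulation remains at the pre-dose sample. The tests are declared descriptive, so the risk is one of misinterpretation rather than of a failed confirmatory claim.

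**What to change.** For the cohort already on IFN-β:

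1. Record hours since the last injection, and the earlier product and dose.
2. Make the absolute post-dose level the main summary, shown with the pre-dose level. It is not free of carry-over, but it describes what standard treatment reaches, which is the intended benchmark.
3. Present the change as an increment over the on-treatment value, by time since the last injection, and separately from the naive RRMS patients.
4. State that a difference in raw change between this cohort and the naive cohorts will not be interpreted as a difference in response to IFN-β.

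Separately, reconcile the statement in Therapy that these patients receive a single dose while in the study with the screening window of up to 14 days and with treatment described as ongoing, so that it is clear whether routine injections continue before the study dose. Which arrangement applies is for the sponsor and investigator.

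The cost is a few CRF fields, one extra table and a more limited conclusion from the change in this cohort. Sample size and blood sampling are unaffected.

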### Exclusion criteria

The main exclusion criteria comprise of: known allergy or hypersensitivity to IFN-β or ingredients of the injection solution; condition or disease which at the investigator’s discretion do not fit with the study; known or persistent abuse of medication, drugs or alcohol; current use of cortisone preparation; subjects with reproductive potential who do not accept to use contraception during the trial and 3 months thereafter or women who are pregnant or breast-feeding; prior malignancy except for adequately treated carcinoma in situ of the cervix or non-melanoma skin cancer unless prior malignancy was diagnosed and definitively treated at least 5 years previously with no subsequent evidence of recurrence the subject at the discretion of the investigator; prior chemotherapy, systemic or local treatment with DNA-damaging and immune-modulating agents, tyrosine kinase inhibitors or anti-angiogenic agents for any cancer; history of major depression, suicide attempt in the past, ongoing suicidal thoughts; history of epileptic seizures under medical therapy with antiepileptic drugs; cardiac insufficiency (NYHA III or IV) cardiomyopathy, significant cardiac dysrhythmia, unstable or advanced ischemic heart disease, or significant hypertension at rest (blood pressure > 180/110 mmHg); HIV, Hepatitis B or C infection or any relevant infectious disease which might interfere with the study procedures and results (at the discretion of the investigator).

